**Methods:**

This single-blind, randomized, comparative efficacy study will involve 96 participants with chronic stroke. Participants will be randomized into bilateral RT+MT, bilateral RT+BAT, and bilateral RT+IOT groups and receive 18 intervention sessions (90 min/day, 3 d/week for 6 weeks). The outcomes will include the Fugl-Meyer Assessment, Stroke Impact Scale version 3.0, Medical Research Council scale, Revised Nottingham Sensory Assessment, ABILHAND Questionnaire, and accelerometer and will be assessed at baseline, after treatment, and at the 3-month follow-up. Analysis of covariance and the chi-square automatic interaction detector method will be used to examine the comparative efficacy and predictors of outcome, respectively, after bilateral RT+MT, bilateral RT+BAT, and bilateral RT+IOT.

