### Movement-based robotic priming

Motor priming in neurorehabilitation can be defined as a change in behavior on the basis of previous stimuli and is an emerging strategy to facilitate motor relearning [4]. As a therapeutic possibility, bilateral RT may be used as a bilateral priming technique in combination with different task-oriented therapies [17], such as MT and BAT, and may yield differential benefits. This project aims to investigate the comparative efficacy of these different combinatory approaches based on the tenet of bilateral movement practice approach. The primary goal of the comparative efficacy trial will be to explore the differential effects of the hybrid intervention of RT combined with MT and BAT on motor function, daily function, sensory, mobility, life quality, self-efficacy, and motor control strategy in stroke patients. The retention effects and possible delayed response of the interventions will be examined at 3-month follow-up. The second aim of this study will be to identify predictors of changes in quality of life after the interventions using the Chi-square Automatic Interaction Detector (CHAID) method

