### Sample size estimation

No published research to date has compared the effects of bilateral RT+MT, RT+BAT, and RT+impairment-oriented training (IOT). Thus, the sample size required for this project was calculated and estimated based on our published studies [8, 21, 22].

In a previous study, we randomized 21 stroke patients to two treatments: RT+task-oriented training and RT+IOT [21]. Between-group analyses revealed small to large effects on the FMA (*p* = 0.01, *η*^2^ = 0.43), Stroke Impact Scale (*p* = 0.046, *η*^2^ = 0.29), and Medical Research Council scale (*p* = 0.98, *η*^2^ < 0.01), respectively.

An additional 21 stroke patients were randomized to receive RT+BAT or RT [8]. Between-group analyses revealed small to large effects on the FMA (*p* = 0.82, *η*^2^ = 0.003) and Goal Attainment Scale total scores (*p* > 0.01, *η*^2^ = 0.633). We randomized 23 stroke patients to two treatment groups: MT and BAT [22]. Between-group analyses revealed small to large effects on the FMA (*p* = 0.67, *η*^2^ = 0.009) and Stroke Impact Scale Version 3.0 total scores (*p* = 0.02, *η*^2^ = 0.165), respectively.

In addition, we used the pilot data of three groups for the FMA proximal UE score (*p* = 0.051, *η*^2^ = .114) to calculate sample size. In light of our previous findings [8, 21, 22], we estimate that to achieve a statistical power of 0.80 with a two-sided type I error of 0.05 and with an estimated dropout rate of 10% to 15% at the 3-month follow-up, a total sample size of 96 with 32 subjects for each group will be sufficient.

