### Statistical analyses

One-way analysis of variance and *χ*^2^ will be used to analyze differences in baseline characteristics and outcome measures among the three groups. Analysis of covariance will be conducted at the assessments, followed by a post hoc analysis using the Bonferroni test to identify the direction of the effects. Statistical significance will be set at 0.05 for all comparisons. We will use the “pretest” performance as a covariate to parcel out the possible confounding effects of differences in baseline performance. The group will be the independent variable and the posttest and follow-up test performance will be the dependent variable. The missing data will be adjusted based on the last observation carried forward (Herman, 2009). Partial eta squared (*η*^2^) will also be estimated to determine the group difference for each outcome measure. Predictors of intervention outcomes will be estimated with the chi-square automatic interaction detector method. Data analyses will be performed using the SPSS Statistics 18.0 software (IBM Corp, Armonk, NY).

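### Carrying the last observation forward pulls the 3-month result toward the posttest result, at the visit that is meant to show retention and delayed response

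*Protocol article*

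**What the plan says.** The Statistical analyses section of the protocol article gives one rule for missing data: "The missing data will be adjusted based on the last observation carried forward". It does not restrict the rule to a visit or an outcome. The analysis is by covariance, in which "the posttest and follow-up test performance will be the dependent variable" and the pretest score is the covariate.

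The outcomes "will be assessed at baseline, after treatment, and at the 3-month follow-up", so the posttest is the only post-treatment value that can be carried to 3 months. The aims, under Movement-based robotic priming, give that visit its purpose: "The retention effects and possible delayed response of the interventions will be examined at 3-month follow-up". The Sample size estimation section allows for "an estimated dropout rate of 10% to 15% at the 3-month follow-up".

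**The concern.** Last observation carried forward (LOCF) assumes that nothing changes after the last visit attended. Here, whether something changes after the posttest is the question put to the 3-month visit. For each patient lost between the two visits, the rule supplies the answer: full retention and no delayed response. For a patient lost before the posttest it supplies a different one: no gain at either visit.

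At stake are the 3-month estimates for the primary outcome (the upper-extremity Fugl-Meyer score) and for every secondary outcome handled in the same way. The within-arm account of retention is distorted whenever the true course after treatment is not flat. The comparison between arms is distorted when that course differs between arms, or when it is not flat and dropout is unequal. The article fixes this rule itself, so it is not a detail left to an unseen analysis plan.

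**Working it through.** **The plan's own figure first.** Inputs from Sample size estimation: three-group pilot η² = 0.114, "to achieve a statistical power of 0.80", "with a two-sided type I error of 0.05", dropout 10% to 15%, total 96.

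- f² = 0.114 / 0.886 = 0.129, so f = 0.359.
- The noncentral F test for three equal groups with λ = f²N needs N = 78 (26 per arm) for power 0.800.
- Inflation: 78 / 0.90 = 86.7, so 87; 78 / 0.85 = 91.8, so 92, or 93 with equal arms.

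The stated 96 is sufficient.

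**How many values are imputed.** 0.10 × 96 = 9.6 and 0.15 × 96 = 14.4, that is 3.2 to 4.8 per arm.

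**Within an arm.** Let r be the true share of the posttest gain retained at 3 months, and d the share of patients lost after the posttest. Assume that those lost had the same average gain as the others. LOCF then reports (1 − d)r + d.

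| True r | Reported, d = 0.10 | Reported, d = 0.15 |
|---|---|---|
| 0 | 0.10 | 0.15 |
| 0.5 | 0.55 | 0.575 |
| 1 | 1.00 | 1.00 |
| 1.5 (delayed gain) | 1.45 | 1.425 |

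The report is right only at r = 1. If the loss occurs before the posttest, the pretest score is carried and both visits shrink: the reported 3-month gain is (1 − d)r of the true posttest gain, for example 0.45 to 0.425 at r = 0.5.

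**Between arms, equal dropout after the posttest.** The LOCF difference at 3 months is (1 − d) × (true 3-month difference) + d × (posttest difference).

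- A difference that arises only at 3 months keeps 1 − d of its size: 85% to 90%.
- A posttest difference that has gone by 3 months still shows at d of its size: 10% to 15%.

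**Between arms, in general.** The bias is d₁ × decay₁ − d₂ × decay₂. The documents give no decay and no arm-specific dropout, so these figures are assumptions:

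- Decay 3 v 1 points, true equality at 3 months, dropout 15% v 15%: 0.45 − 0.15 = 0.30 points.
- Same decay, dropout 20% v 5%: 0.60 − 0.05 = 0.55 points.
- Decay 3 v 3, dropout 20% v 5%: 0.60 − 0.15 = 0.45 points.
- No decay, any dropout: 0.

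Simulation with 32 per arm (assumed SD of gain 4, follow-up noise SD 2) gave about 0.32 and 0.57 for the first two cases, in line with the formula.

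A three-arm simulation used an assumed gain of 5 points, dropout of 5%, 12.5% and 20%, and no true difference. When all gain was lost, the extreme arms differed by about 0.75 points, and type I error was about 0.07 with LOCF against about 0.045 with observed cases. With equal dropout and equal courses, type I error stayed near 0.05.

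**Power without LOCF.** 96 × 0.85 = 81.6 and 96 × 0.90 = 86.4, so about 81 to 86 observed patients. At η² = 0.114 their power is 0.817 to 0.841. Counting all 96 as observed gives a nominal 0.882.

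**The case against.** The strongest reply is that the effect is small and partly assumed. Between 85% and 90% of the 3-month scores are expected to be observed. A bias of 0.30 to 0.55 points on a 66-point scale is about 0.3 to 0.5 of a standard error (0.30 / 1.04 and 0.55 / 1.04, with the simulated standard error of 1.04). Type I error was 0.054 with equal 15% dropout and decay of 3 v 1. It reached about 0.07 to 0.085, in separate simulations, only when that unequal decay was joined to fourfold unequal dropout. The Adherence section plans transport, weekly calls and home visits to limit losses. The posttest comparison is affected only by earlier losses, which the article does not quantify. All of this stands, and it limits the weight of the point. It does not remove the mismatch between the rule and the question put to the 3-month visit.

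A reader might also infer more than the documents support:

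- *That the imputation settles the retention question.* It does so only for the imputed patients.
- *That standard errors are too small because imputed scores count as observed.* In simulation the mean model standard error was 1.04 against an empirical SD of 1.03 (15% v 15%), and 1.04 against 1.06 (20% v 5%). The fault is bias.
- *That any imbalance in dropout biases the comparison.* With a flat course after treatment the formula gives zero, and simulation agreed. Terms can also cancel.
- *That the analysis ignores the posttest when follow-up is missing.* LOCF does use the posttest, but under the assumption of no change.
- *That the lack of a missing-not-at-random sensitivity analysis is a defect.* An analysis plan that is not shown may contain one.

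**Conclusion.** The point holds in a limited form, as a recommended change to the main analysis. LOCF is fixed in the article, and it assumes no change at the visit chosen to detect change. By the plan's own dropout figure it moves the 3-month result 10% to 15% of the way toward the posttest result, provided that the losses fall after the posttest and those lost resemble the others in gain. This needs no imbalance between arms. The between-arm bias of 0.30 to 0.55 points rests on assumed decay and dropout; its direction cannot be known beforehand. The sample size is not called into question.

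**What to change.** In Statistical analyses, replace LOCF in the main analysis with one mixed model for repeated measures. Posttest and 3-month scores are the outcomes. The terms are baseline score, group, time, group × time and baseline × time, with an unstructured covariance for the two visits. Read the group contrasts at each visit from this model. Under missing at random it uses an observed posttest to inform a missing 3-month score without assuming a flat course.

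Multiple imputation under missing at random is an equally acceptable choice. It also keeps in the analysis the patients who have only a baseline score. LOCF may remain at most as a sensitivity analysis.

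The cost is a change of analysis wording. No visit, measurement or patient is added: the allowance for dropout already leaves about 81 to 86 observed patients, with power of 0.817 to 0.841 at the pilot effect. The article reports recruitment as ongoing at submission and foresees interim analyses, so the amendment should be dated and made without sight of results by arm.

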## Discussion

The study goal is to investigate the comparative efficacy of RT+MT, RT+BAT, and RT+IOT after stroke. The outcome measures are selected based on our previous studies [8, 10, 21, 22] and are in line with the International Classification of Function framework to facilitate interpretability of the functional significance of treatment outcomes [34]. According to our previous research [8, 10, 21, 22], hybrid bilateral therapy (RT+MT and RT+BAT) may result in greater recovery of the primary outcome (i.e., FMA) compared with the control condition (RT+IOT). The RT+MT group may improve sensory function more than the RT+BAT and the control groups. In addition, the combined use of subjective and objective assessments would provide more comprehensive information regarding participants’ actual and perceived improvements.

Our hybrid regimens are unique in using bilateral robotic practice as a priming technique to augment bilateral task practice with and without mirror visual feedback. The anticipated benefits of robot-assisted bilateral movement priming in stroke rehabilitation may be associated with balanced excitability between the ipsilesional and contralesional hemispheres [35], positive reorganization in the motor cortex [36, 37], and improvements in later voluntary and complicated task performance [38]. The context-related and goal-directed practice in our treatment protocol may assist the patients to transfer therapeutic gains in clinics to their real-life environment and generalize motor improvements to performance of daily activities [21].

Mirror visual feedback of the unaffected UE is provided when both UEs perform bilateral tasks in the RT+MT group, which is expected to have more improvements in sensory function over the other two groups. It is possible that the illusory visual feedback to be substituted for inadequate proprioceptive input of the affected UE may activate multimodal neurons in parietal cortex [39]. This activation may contribute to improvements in somatosensory deficits [40, 41], which are frequent in patients recovering from stroke [42]. Given the promise of improving sensorimotor outcomes using mirror visual feedback during bilateral task practice, our research will study the therapeutic benefit of RT hybridized with MT relative to the dose-matched comparison treatment.

The findings of this protocol are expected to contribute to the research and development of technology-based stroke rehabilitation that will promote the use of robotic devices for streamlining stroke motor rehabilitation and the use of accelerometers for monitoring activity level in real-life situations. The activity monitors may be useful for providing behavioral feedback to the participants regarding their actual amount of movement. We anticipate that this research of the accelerometer will lead to increased use of self-monitoring in the home environment, which may in turn promote home-based practice by the patients and their caregivers. The findings can be applied to update the evidence-based protocols in the postacute stroke care program and to translate the evidence into practice and health care decision making.

### Protocol version

The 3^rd^ version

### Trial status

At the time of submission, the study is recruiting participants.

## Data Availability

Not applicable.

## Abbreviations

BAT: Bilateral arm training
FMA: Fugl-Meyer Assessment
IOT: Impairment-oriented training
MT: Mirror therapy
RT: Robotic training
UE: Upper extremity
